**Table 3 Tab3:**
[figure not shown]
Measurements and time points

### Primary outcome

*Fatigue severity* is assessed by the subscale fatigue severity of the CIS [38]. The CIS consists of 20 items scored on a 7-point Likert scale and measures four dimensions of fatigue, i.e. fatigue severity, concentration problems, motivation and activity. The CIS-fatigue, the primary outcome, consists of eight items, each item is scored on a 7-point Likert scale. The range of scores is 8 to 56, with a higher score indicating more severe fatigue. The cut-off score for severe fatigue is ≥ 35 [38] on the CIS-fatigue. Previous research supports the reliability and validity of the CIS [38, 61, 62].

### Secondary outcomes

*Limitations in physical functioning* are assessed by the subscale physical functioning of the SF-36 [40] which consists of ten items scored on a 3-point scale. The weighted subscale score ranges from 0 to 100, with a higher score indicating less limitations. A score of ≤ 65 is indicative of substantial limitations in physical functioning [63]. The SF-36 is a reliable and valid instrument [64].

*Social disability* is assessed by the WSAS [41, 65] which consists of five items assessing different domains of functioning, e.g. work and social leisure activities, scored on an 8-point Likert scale. A score of ≥ 10 is indicative of significant functional impairment [41, 65]. The WSAS is a reliable and valid instrument [41, 65.

*Somatic symptom severity* is assessed by the somatic symptoms scale of the Patient Health Questionnaire (PHQ) [66]. The PHQ-15 consists of 15 items referring to somatic symptoms. Each symptom is scored on a 3-point scale with scores of 5, 10 and 15 indicate low, medium, and high symptom severity. Research supports the reliability and validity of the PHQ-15 [66].

*Problems concentrating* are assessed by the subscale concentration of the CIS which consists of five items scored on a 7-point Likert scale. The scores range from 5 to 35, with a higher score indicating more difficulties in concentrating.

### Demographics and patient characteristics

The demographic characteristics include age, sex, relationship/cohabitation status, level of education and employment status. Patient characteristics include lenght, weight, morbidities, hospital/ ICU admission, start date of COVID-19 symptoms, date of COVID-19 test, type of COVID-19 test, physician visit for COVID-19 and vaccination status. All of the characteristics are assessed by self-report during screening. Vaccination status is also assessed at T1.

### Other study outcomes

*Activity:* An actigraph is used to assess the participant’s level of physical activity. The actigraph is worn around the wrist for 14 consecutive days and nights for a reliable estimate of daily activity for 12 full days. The actigraph has been shown to be a reliable and valid instrument for the assessment of physical activity [53, 67].

*Sleep parameters:* During the 14 days participants wear the actigraph, a sleep diary [68] is also completed daily, if possible within one hour of getting out of bed in the morning. Participants have to fill in (1) the time they go to bed (in hours and minutes), (2) the time they try to fall asleep, (3) the sleep onset latency, (4) time awake at night, (5) time out of bed, (6) time of waking-up, (7) time of getting out of bed and (8) a rating of the sleep quality (scale 0–10) [69]. Sleep problems are also assessed by the ISI [48] and the subscale sleep-rest of the Sickness Impact Profile (SIP) [70, 71].

*Fatigue-related behaviours, cognitions and emotions*: Based on the cognitive behavioural model for fatigue in CFS and fatigue in other long-term conditions, several fatigue-related behaviours, cognitions and emotions are assessed. These are dysfunctional beliefs assessed by the J-FCS [49], IMQ [50] and the SES [51, 52, social support assessed by the SSL-D and SSL-I [54, 55], problems with processing assessed by the IES [56, 57], and pain assessed by the subscale pain of the SF-36 [40]. To assess COVID-19 related worries, we adapted the Cancer Worry Scale [58]. The resulting COVID-19 Worry Scale (COWS) consistently refers to COVID-19 instead of cancer. For participants randomised to CBT, the T0 actigraph data, sleep data and questionnaires about fatigue-related behaviours, cognitions and emotions are used to tailor *Fit after COVID* to the individual (see Intervention paragraph).

*Other relevant parameters:* The criteria for CFS are assessed by the US Centers for Disease Control and Prevention (CDC) criteria revised in 2003 [72]. Mental health is assessed by the patient health questionnaire, somatic, anxiety and depressive symptoms (PHQ-SADS) [73]. Social functioning is assessed by the subscale social functioning of the SF-36 [40] and the SIP [71]. Illness perceptions are assessed by the Brief Illness Perception Questionnaire (B-IPQ) [74, 75]. Illness attributions are assessed by the Causal Attribution List (CAL) [76]. Responses to symptoms are assessed by the Cognitive Behavioural Responses to Symptoms Questionnaire (CBRSQ) [77, 78]. Fear of movement is assessed by the Tampa Scale of kinesiophobia (TSK) [79]. Invalidation experiences are assessed by the Illness Invalidation Inventory (3*I) [80]. Resilience is assessed by the Brief Resilience Scale (BRS-6) [81, 82]. Expectations about treatment are assessed by the Treatment Outcome Expectations Questionnaire (TOEQ) [83]. All study parameters are assessed as shown in Table 3.

### Primary and secondary objectives

The primary objective is to investigate whether CBT will lead to a significantly lower mean fatigue severity score measured with the CIS-fatigue across follow-up visits T1 and T2 as compared to care as usual.

Secondary objectives are to investigate whether CBT as compared to care as usual will result in:
A smaller proportion of patients meeting the cut-off score for severe fatigue (i.e. caseness as defined by a CIS-fatigue score of ≥ 35) at follow-up assessments T1 and T2 separately;A higher proportion of patients no longer meeting the cut-off score (as defined in a) and additionally, reporting a clinical significant change (i.e. Reliable Change Index (RCI)) [84] in fatigue severity at follow-up assessments T1 and T2 separately;A smaller proportion of patients with chronic fatigue (i.e. caseness as defined in a) and self-reported duration of fatigue of 6 months or longer at T1 and T2 separately;Significantly higher mean physical functioning as assessed with the SF-36 across follow-up assessments (T1 and T2);Significantly lower mean level on the WSAS across follow-up assessments (T1 and T2);Significantly lower mean level of somatic symptoms as assessed with the PHQ-15 across follow-up assessments (T1 and T2); andSignificantly lower mean level of cognitive symptoms as assessed with the subscale concentration problems of the CIS across follow-up assessments (T1 and T2).

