a) Diagnosed with symptomatic COVID-19, confirmed by a positive PCR for SARS-CoV-2 *or* another positive NAAT test (RT-PCR, LAMP, TMA or mPOCT) *or* positive SARS-CoV-2 serology *or* a positive Antigen test *or* CORADS 4 or 5 on CT-scan. b) Three up to including 12 months after being diagnosed with COVID-19 or after hospital discharge in case the patient was admitted. c) Severe fatigue, operationalised as a score of ≥ 35 on the subscale fatigue of the Checklist Individual Strength (CIS) [38]. Fatigue started with or increased substantially directly after the onset of symptoms of COVID-19, as reported by the patient and confirmed by their GP or treating physician. d) Limitations in physical functioning operationalised as a score of ≤ 65 on the Short Form Health Survey (SF-36) [40] or social disability operationalised as a score of ≥ 10 on the Work and Social Adjustment Scale (WSAS) [41]. e) Age of 18 years or older. f) Sufficient command of the Dutch language.	a) Known psychiatric or somatic condition that can explain the fatigue. Screening for somatic condition is done by the referring physician or the patient’s GP in case of self-referral. Participants are screened for the presence of post-traumatic stress disorder (PTSD) with the PTSD Checklist for DSM-5 (PCL-5) [42] and for the presence of depressive disorder with the Beck Depression Inventory for Primary Care (BDI-PC) [43, 44]. When the score on the BDI-PC is ≥ 4 or the score on the PCL-5 is ≥ 33, the Mini-International Neuropsychiatric Interview (M.I.N.I.) [45] is conducted to determine if patients meet the criteria of PTSD or a depressive disorder. b) Current participation in a multi-disciplinary rehabilitation programme aimed to ameliorate the consequences of COVID-19. c) Objective hypoxaemia in rest for which oxygen therapy at home is indicated.

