### Statistical analyses

Descriptive statistics (i.e. participant characteristics) will be presented in tables, with separate columns for participants randomised to CBT vs. participants randomised to care as usual. Categorical variables (e.g. sex, relationship status) will be presented in participant numbers (*n*) and percentages (%). Continuous variables (e.g. age, CIS-fatigue baseline score) will be presented in means and standard deviations (SD) or, if appropriate due to skewness of data, as median with its interquartile range. Participant numbers, dropout and reasons for dropout will be presented in the study flow-chart. In all analyses, two-sided *p* values of < 0.05 are considered to indicate statistical significance. All analyses will be conducted in SPSS.

Change in fatigue scores between T0 and T1 for each individual participant will be shown in a figure using the Leeds RCI calculator [86]. This figure will show whether the change was clinically significant and reliable, or reliable only, and if there was no change or a deterioration in fatigue.

The primary study parameter will be analysed according to intention-to-treat, i.e. all randomised participants will be included in the analysis and they are analysed in the group to which they were randomly allocated. The primary hypothesis will be tested using a mixed linear model. The model will include T1 and T2 fatigue severity score as a dependent variable, condition (CBT vs. care as usual), time (T1, T2), condition by time interaction as fixed effects, a random intercept and the fatigue severity score at baseline as covariate. It will be examined if the main effect of condition from the mixed linear model, i.e. the mean difference in CIS-fatigue scores across T1 and T2 while controlling for baseline fatigue, is statistically significant. If the main effect of condition is found to be statistically significant, the statistical significance of the between group differences at the separate time points (T1 and T2) will be interpreted.

Cohen’s d effect sizes will be calculated by dividing the parameter estimate for the mean difference in CIS-fatigue scores between both conditions from the mixed linear model by the pooled standard deviation of both conditions combined. Effect size magnitudes will be interpreted as small (0.2 to 0.5), medium (0.5 to 0.8) and large (greater than 0.8) [87].

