To explore the robustness of our findings from the primary analysis, four sensitivity analyses will be conducted. First, per protocol analysis will be conducted. Treatment completion will be operationalized in two ways, i.e. by including (a) participants who have filled out the treatment goals and opened the standard modules of the intervention and (b) participants who have completed the intervention according their therapist.

Second, as the primary outcome consists of the mean CIS-fatigue score across T1 and T2, the extent to which our result would change if based on a single time point will be explored. Therefore, the analysis with the CIS-fatigue score at T1 as a dependent variable and with the CIS-fatigue score at T2 as a dependent variable adjusted for CIS-fatigue score at baseline using analysis of covariance will be repeated. For each of the time points Cohen’s d effect sizes will be calculated.

Third, the extent to which dyspnoea at T0, disease severity, time since diagnosis of COVID-19, age and sex have an impact on the primary outcome will be explored, and whether this impact differs between CBT and care as usual. These analyses will be conducted by including these variables and their interaction-terms with condition as covariates in the mixed linear models.

Fourth, missing values will be replaced with multiple imputation using chained equations and the data will be reanalysed. The imputation model will include all baseline sociodemographic and clinical characteristics assessed at baseline and follow-up measurements. A total of five data sets will be imputed and pooled according to Rubin’s rule.

Secondary outcomes will also be analysed according to intention-to-treat. For T1 and T2, it will be determined if there is a clinical meaningful improvement in fatigue, defined as a RCI [84] of more than 1.96 and a decrease of the fatigue level to a normal range (i.e. a score of < 35 on the CIS-fatigue). For secondary outcomes that are dichotomous, separate logistic regression analysis will be done for T1 and T2. For secondary outcomes that are continuous (i.e. physical functioning, work and social adjustment, somatic symptoms, cognitive symptoms), differences between CBT and care as usual will be analysed using mixed linear models as described above.

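### The logistic regressions for the dichotomous fatigue outcomes are stated without baseline CIS-fatigue, although the other between-arm fatigue models adjust for it

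*Protocol article*

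**What the plan says.** Inclusion criterion c (Protocol article, Table 1) requires "Severe fatigue, operationalised as a score of ≥ 35 on the subscale fatigue of the Checklist Individual Strength (CIS"). In Primary and secondary objectives, the first secondary objective, (a), uses the same threshold: "caseness as defined by a CIS-fatigue score of ≥ 35) at follow-up assessments T1 and T2 separately". Objective (b) is stricter. It asks for those "no longer meeting the cut-off score (as defined in a) and additionally, reporting a clinical significant change (i.e. Reliable Change Index (RCI")), which Statistical analyses makes concrete as an "RCI [84] of more than 1.96 and a decrease of the fatigue level to a normal range (i.e. a score of < 35"). Objective (c) reuses the caseness of (a) and adds a fatigue duration of at least 6 months.

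On the models, Statistical analyses says:

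- Primary outcome: a mixed linear model with "a random intercept and the fatigue severity score at baseline as covariate".
- Sensitivity analyses at T1 and at T2: analysis of covariance, adjusted for baseline CIS-fatigue.
- Continuous secondary outcomes: "differences between CBT and care as usual will be analysed using mixed linear models as described above", which carries the baseline adjustment over.
- Dichotomous secondary outcomes: "For secondary outcomes that are dichotomous, separate logistic regression analysis will be done for T1 and T2". No covariate is named.

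**The concern.** Everyone enters at 35 or more, and caseness is later judged at 35. A participant who starts at 36 needs a fall of 2 points to leave the category; one who starts at 52 needs a fall of 18. The T0 score is therefore likely to be a strong predictor of caseness, and it is already collected. A logistic model that ignores it tests the arm difference with less power than the data allow. The article states baseline adjustment for its other between-arm models of fatigue, so the text reads as if these regressions are unadjusted.

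A second, smaller matter is interpretation. Selection at a cut-off combined with ordinary score variation will put some participants below 35 without real change. Objective (a) has no minimum-change condition, so the proportion below 35 within one arm cannot be read as the proportion who improved.

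**Working it through.** **1. The plan's own figure.** From Sample size calculation: SD 12, T1–T2 correlation 0.4, difference 6, two-sided 0.05, power 80%.

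- SD of the mean of two visits = 12 × √((1 + 0.4)/2) = 10.04.
- n per arm = 2 × (10.04 × (1.96 + 0.842)/6)² = 43.95, so 44. With the t distribution, 45 per arm gives 80.1%.
- 45/0.80 = 56.25, so 57 per arm and 114 in total.

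The figure reproduces. It concerns the continuous primary outcome; no power is stated for caseness.

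**2. Power for caseness at one visit, with and without T0 CIS-fatigue.** The protocol gives no baseline mean and no baseline to follow-up correlation, so both are assumed.

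- Baseline: about normal with mean 45 and SD 6, limited to 35–56.
- Follow-up: SD 12, a fall of 4 points under usual care and a further 6 under CBT, rounded and limited to 8–56.
- A case is a score of 35 or more. There are 45 per arm, tested with a logistic Wald test at two-sided 0.05, over 5,000 simulated trials per correlation.

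Caseness is about 71% under usual care and 51% under CBT.

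| Assumed correlation | Unadjusted power | With T0 score | Gain (points) |
|---|---|---|---|
| 0.2 | 0.437 | 0.459 | 2.2 |
| 0.4 | 0.446 | 0.499 | 5.3 |
| 0.5 | 0.437 | 0.512 | 7.5 |
| 0.6 | 0.457 | 0.556 | 9.9 |

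A separate run of this comparison gave 0.44–0.45 unadjusted and 0.47, 0.49, 0.52 and 0.56 adjusted, which agrees within simulation error.

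In another set-up, baseline is a normal distribution with SD 12 cut off at 35, and the correlation applies before that selection. The gains are smaller:

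- source mean 40, correlation 0.4: 0.467 to 0.489;
- source mean 40, correlation 0.6: 0.501 to 0.535;
- source mean 45, correlation 0.4: 0.401 to 0.417.

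That is about 2 to 3 points. With no treatment effect, rejection in this set-up is 3.7–5.9% unadjusted and 4.0–5.5% adjusted, so type I error is not the issue.

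These runs concern caseness, objective (a). Objectives (b) and (c) were not simulated.

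**3. Can the share crossing 35 without real change be estimated?** Two models with no true mean change:

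- Normal with SD 12 cut off at 35, source mean 30 to 45: at correlation 0.4, 48%, 36%, 24% and 15% for means 30, 35, 40 and 45; at correlation 0.9, 19%, 14%, 10% and 6%.
- Measurement error only, baseline SD 4–6 and standard error of measurement 2–5: 5–15% at an observed baseline mean of 40, 1–5% at 44 and 0–1% at 48.

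The answer runs from 0% to 48%. The only stated correlation, 0.4, is between T1 and T2, six months apart, and includes real change. Taken as pure retest reliability it would imply a standard error of measurement of 12 × √0.6 = 9.3 points. An RCI above 1.96 would then need a change of 1.96 × √2 × 9.3 ≈ 26 points. That is hard to reconcile with the protocol's description of the CIS as reliable.

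**The case against.** **The article may condense the covariate list.** Naming no covariate does not prove that the model is unadjusted, since the full protocol and any analysis plan are not shown. This stands as a caution. However, the same section states the adjustment for the primary model and for the single-visit analyses, and carries it to the continuous secondary outcomes by reference. The logistic sentence has no such reference, so it needs the clause.

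**The gain is modest and the outcome is secondary.** This also stands. The trial is powered on the continuous outcome, and caseness remains underpowered with adjustment. But the covariate costs nothing to collect.

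**A reader might infer that noise alone produces many of those no longer severely fatigued.** The documents do not support this. They give neither baseline mean nor retest reliability, and the share ranges from 0% to 48% with the assumptions made.

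**A reader might infer that the comparison of arms is distorted.** It is not. Both randomised arms have the same expected share of such crossings, and objective (a) is worded as a comparison with usual care.

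**A reader might infer that (a) must be replaced by a sustained definition.** Objective (b) already pairs the cut-off with reliable change, and Statistical analyses adds a figure classifying each participant's change from T0 to T1. Requiring a score below 35 at both visits would discard late improvers. Comparing a small individual fall with the 6-point figure is also loose, because the sample-size section uses 6 points as a difference between group means.

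**Conclusion.** The point holds as a gap in the stated model. The dichotomous fatigue outcomes are the between-arm fatigue analyses for which no baseline adjustment is given, and the threshold in (a) is the entry threshold. The cost is about 2 to 10 percentage points of power for caseness at one visit. This rests on 45 per arm, a 6-point effect, follow-up SD 12 and assumed baseline to follow-up correlations of 0.2 to 0.6; the lower end is more likely if the correlation among enrolled participants is weak. There is no bias and no type I error problem, and the primary conclusion is unaffected.

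On interpretation, the supportable statement is narrow. Some participants may cross 35 without real change, the share cannot be estimated from the protocol, and so the proportion below 35 in one arm should not be presented as a recovery rate.

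**What to change.** 1. In Statistical analyses, state that the T1 and T2 logistic regressions for the dichotomous fatigue outcomes include T0 CIS-fatigue as a covariate.
2. State that objective (a) is interpreted only as a contrast between arms, and that statements about individual improvement rest on objective (b), a score below 35 plus RCI above 1.96.
3. Optionally, add caseness resolved at both T1 and T2 as a sensitivity analysis, alongside (a) and not in its place.

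The cost is wording only, with no new data, visits or participants. The odds ratio becomes conditional on baseline and is no longer the one computed directly from the two observed proportions, so those should be reported beside it. The optional both-visits analysis needs data at both visits and so loses somewhat more to missing values. The wording should be settled before anyone analyses outcomes by arm.

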### Adverse events (AE’s)/serious adverse events (SAE’s)

At T1, all participants are asked to report if they experienced new symptoms or an increase in existing symptoms during CBT or care as usual. All AE’s reported by the participant or observed by the therapists or research staff are recorded and reported.

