### Care as usual

After randomisation, participants in the care as usual condition have no access to *Fit after COVID* during the study, but are not restrained from using any form of care for fatigue or other COVID-19 related symptoms. Care as usual for post-COVID-19 patients can entail follow-up contacts with their treating physician or GP, physical training, occupational therapy or rehabilitation. At T1, all participants are questioned about the care they received since baseline assessment. Participants who are still severely fatigued, i.e. a score of ≥ 35 on the CIS-fatigue at T2, and voice a care need can be referred for CBT for severe fatigue; this will be provided by the ECCF of the Amsterdam UMC.

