### Monitoring and auditing

This study is subject to on-site monitoring in accordance with the quality assurance advice of the Dutch Federation of University Medical Centres regarding research involving human subjects [85]. On-site monitoring is based on the risk classification negligible. The investigator will submit a summary of the progress of the trial to the ethics committee once a year. Information will be provided on the date of inclusion of the first subject, numbers of subjects included, numbers of subjects that have completed the trial, SAEs and amendments.

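### New or worsened symptoms and other care are described as asked about only at T1, and individual deterioration is displayed only to T1, although the primary effect runs to T2; therapist-observed events can arise only in the CBT arm

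*Protocol article*

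**What the plan says.** All references are to the protocol article.

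- **Solicited harms** (Adverse events section): "At T1, all participants are asked to report if they experienced new symptoms or an increase in existing symptoms". The question is the same in both arms and is tied to the treatment period.
- **Other adverse events** (same section): "All AE’s reported by the participant or observed by the therapists or research staff are recorded and reported". No end date is given. Under Monitoring and auditing, serious adverse events form part of the annual summary to the ethics committee.
- **Other care** (Care as usual): "At T1, all participants are questioned about the care they received since baseline assessment". The same section leaves care-as-usual participants free to use any care for their symptoms.
- **Individual change** (Statistical analyses): "Change in fatigue scores between T0 and T1 for each individual participant will be shown in a figure using the Leeds RCI calculator". The figure's categories include deterioration. The reliable-change classification planned for both T1 and T2 concerns improvement only.
- **Primary effect** (Primary and secondary objectives; Statistical analyses): the mean CIS-fatigue difference across T1 and T2.
- **Timing** (Procedure): T1 is 19 weeks after randomisation and T2 is 6 months after T1.

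**The concern.** Benefit and harm are followed over different windows. Benefit is averaged over T1 and T2, and individual improvement is classified at both. The described harms question, the described care question and the only display of individual deterioration stop at T1.

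The protocol itself gives reasons to look beyond T1. The Background reports relapse in a subgroup after CBT in some studies. The Discussion says a fading effect might justify booster sessions. Current multidisciplinary rehabilitation is an exclusion criterion, yet rehabilitation and physical training are listed as possible usual care. If the difference between arms narrows from T1 to T2, it will matter whether CBT participants relapsed or controls took up other care, and nothing in the text says care use after T1 will be known.

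The second issue is ascertainment. Trial therapists follow CBT participants for 17 weeks, register each contact and discuss every case in supervision every two weeks (Adherence and treatment integrity). Care-as-usual participants have no matching observer. If therapist-observed events go into one count with participant reports, the arms are measured with different instruments.

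**Working it through.** The plan gives no figure on this point, and no sample-size or error-rate figure depends on it. The check compares the sections and does one piece of arithmetic.

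**1. Length of the window.** T1 is at week 19 (Procedure). T2 is 6 months later, taken here as 26 weeks.

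- T2 = 19 + 26 = week 45
- Share of controlled follow-up after T1 = 26 / 45 = 57.8%, about 58%

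**2. What is described in each period.**

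| Item | Randomisation to T1 | T1 to T2 |
|---|---|---|
| Question on new or worsened symptoms | Yes, both arms | Not described |
| Question on care received | Yes, both arms | Not described |
| Unsolicited adverse events | Yes | Yes (no stated cut-off) |
| Serious adverse events in annual summary | Yes | Yes |
| CIS-fatigue, SF-36 physical functioning, WSAS, PHQ-15, CIS-concentration | Yes | Yes, at T2 |
| Reliable improvement classified | At T1 | At T2 |
| Individual deterioration displayed | T0 to T1 | Not planned |

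So the gap lies in two prompted questions and one display. It does not extend to all harms information. CIS-fatigue is measured at T2, so deterioration by T2 can be derived without new data.

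**3. Observation by arm.** The named sources are participants, therapists and research staff.

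- Participants: both arms (57 + 57 = 114 planned).
- Research staff: both arms.
- Therapists: the CBT arm only, 57 / 114 = 50% of those randomised.

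**4. Illustration of unequal detection.** The detection rates below are assumed and are not in the document. With the same true event risk p in both arms and detection probabilities s0 (care as usual) and s1 (CBT), the apparent risk ratio is (p × s1) / (p × s0) = s1 / s0, whatever p is.

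- s0 = 0.60, s1 = 0.70: 0.70 / 0.60 = 1.17
- s0 = 0.60, s1 = 0.80: 0.80 / 0.60 = 1.33
- s0 = 0.60, s1 = 0.90: 0.90 / 0.60 = 1.50

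This shows how extra detection alone could look like excess harm from CBT. It does not estimate the effect in this trial.

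**5. Room to change.** Recruitment began in November 2020 (Trial status). Counting 45 weeks (315 days) from 1 November 2020 gives about 12 September 2021 for the earliest T2. The register search is dated July 2021 and 89 participants had been randomised at submission. The submission date is not stated. If it came soon after the search, few or no T2 assessments had been made.

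**The case against.** Three stronger readings are tempting, and the document supports none of them.

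- **That harms are not collected after T1.** Events reported by participants or "observed by the therapists or research staff are recorded and reported", with no cut-off, and serious events are summarised yearly. At T2 both arms complete the fatigue, functioning and somatic-symptom scales, so average worsening on those measures is compared between arms. What lacks a described prompt is an open question about new or worsened symptoms.
- **That the T2 half of the primary contrast cannot be interpreted without care-use data.** The comparator is deliberately unrestricted usual care, analysed by intention to treat. Later care is part of what is being compared, so the randomised T2 difference stays valid. Care data would help to explain it.
- **That the adverse event comparison is biased as planned.** The article lists sources but specifies no pooled count and no between-arm test of harms. The T1 question goes to everyone, so a symmetric comparison is already available. The problem arises only if the sources are mixed.

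A further objection carries weight. Table 3, the measurement schedule, is not visible in the text reviewed, and the full protocol is not at hand. A T2 item on symptoms or care therefore cannot be excluded. Against this, the text names time points for measures that are limited to some assessments, such as actigraphy, and it places both questions at T1. That makes a T2 item less likely but does not rule it out, so the request for new items must be conditional.

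It can also be said that the interval shown in a descriptive figure is a reporting choice for the analysis plan. That is fair for the figure alone. But the article commits to classifying improvement at both time points while showing deterioration at one, and that imbalance is cheap to remove.

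**Conclusion.** The point holds in a limited form. As described, new or worsened symptoms and care received are asked about systematically only at T1, and individual deterioration is displayed only to T1, while the primary effect and the classification of improvement extend to T2. About 58% of the controlled follow-up (26 of 45 weeks, taking 6 months as 26 weeks) has no described question of either kind.

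Therapist-observed events are an extra source in the CBT arm only. A mixed between-arm count would not be like for like. The extra source by itself would tend to raise the CBT count, but by an amount the document does not allow anyone to calculate.

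The primary test, its error rate, the sample size and the validity of the T2 comparison with care as usual are unaffected. What is weakened is the balance between benefit and harm reporting and the ability to explain a change in effect between T1 and T2. The statement about missing T2 questions rests on the running text and falls away if Table 3 or the full protocol includes them. The points about the deterioration display and about event sources do not depend on Table 3.

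**What to change.** 1. **Deterioration.** Classify reliable deterioration at T1 and T2 with the same reliable-change threshold as for improvement (1.96), in the opposite direction. Tabulate it by arm with denominators, and add a T0–T2 panel to the figure. The CIS-fatigue data are already collected, so this costs only analysis time.
2. **Source of events.** Base the between-arm harms comparison on the question asked of all participants. List events observed by therapists or research staff separately, by source and arm. This needs a source label on each event record and a sentence in the analysis plan. It does not remove reporting differences that come from participants knowing their allocation.
3. **T2 questions.** Check Table 3 and the full protocol. If the items are absent at T2, add the symptom question and the care-received question to the online T2 questionnaire in both arms, each covering the time since T1. This takes a minor amendment and makes the questionnaire slightly longer. Anyone already past T2 will lack the items, and the report should say how many.
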